### Study population and recruitment

The study population will consist of two groups: a.) healthcare providers, comprising of district and health facility managers, nurses, health information officers, staff involved in data collection at facility and district levels, program managers, monitoring and evaluation officers responsible for each of the seven sub-districts (strata) in the uMgungundlovu district, and b.) AGYW aged 15–24 years and ABYM aged 15–35 years old who test HIV-positive during the routine facility-based, school-based, and community-based HIV testing services. This cohort will be recruited and followed up at one month using questionnaires and at 6 months through routine data. Eligible participants will be considered based on the inclusion and exclusion criteria listed in Table 1.

**Table 1 pone.0271942.t001:** Eligibility criteria for the SHeS’Cap-Linkage study in uMgungundlovu district, KwaZulu-Natal, South Africa, 2021–23.

Inclusion criteria	Exclusion criteria
• Have accepted an HIV test in one of the participating service delivery points from July 2021 to June 2022	• Test HIV-negative on the day of recruitment.
	• No access to a cellphone
• Have access to a cell phone and willingness to provide contact details (required for follow up).	• Unwilling to provide contact details
	• Adolescents <15 years of age
• Be 15–24 years old for AGYW, or 15–35 years old for ABYM.	• Young women over 24 years of age, and men over 35 years of age
• Be seropositive based on HIV rapid test results on the day of recruitment.	• SDPs that don’t provide HIV services
• Be able and willing to provide written informed consent.	• Healthcare providers not involved in implementing the Universal Test and Treat program
• SDPs providing HIV services	
• Healthcare providers involved in implementing the Universal Test and Treat program in selected SDPs	

Participants will be enrolled in the study as they await HIV testing in participating primary health care health facilities, schools and community-level HIV testing and treatment points (described collectively as SDPs). Upon enrolment, they will be grouped into two distinct cohorts for analysis:

Newly enrolled AGYW and ABYM who test HIV-positive in a participating SDP on the day of enrolment during the 12 months data collection period (current protocol).Newly enrolled AGYW and ABYM who test HIV negative on the day of enrolment (SHeS’Cap-PrEP cohort) [21].

Participants will be followed up at 1 and 6 months after enrolment using quantitative and qualitative data collection methods. Data on the HIV testing experience of AGYW and ABYM will be collected cross-sectionally, whereas the linkage and retention data will be monitored prospectively over six months using routine data. In addition, health service and system contextual factors that may influence linkage to and retention in HIV care in participating SDPs will be investigated. Data collection will be over a 24-month period (August 2021 to July 2023). AGYW and ABYM will be recruited at selected SDPs and followed up for 7 months using quantitative and qualitative data collection methods.

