## Materials and methods

### The objectives of the study are

To describe the socio-demographic characteristics of AGYW (15–24 years) and ABYM (15–35 years) newly diagnosed with HIV who access HIV testing services in the uMgungundlovu district of KwaZulu-Natal, and to compare service delivery models.To describe the HIV testing experiences of AGYW and ABYM newly diagnosed with HIV in the uMgungundlovu district, comparing experiences across service delivery models.Among HIV-positive AGYW and ABYM, to quantify linkage to and retention in HIV care across different service delivery models, and to describe the factors associated with linkage to and retention in HIV care and health impacts thereof, in the uMgungundlovu district.To identify the mechanisms (reasoning and decision-making) and context (individual, structural social and health systems factors) that influence AGYW’s and ABYM’s uptake of HIV treatment and care services to describe the relative success of different HIV treatment service delivery models.

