### Study design

The SHeS’Cap-Linkage study, which compliments the SHeS’Cap-PrEP study [21], is a sequential, explanatory, mixed methods study that will be conducted at 22 purposively selected HIV testing and treatment service delivery points (SDPs). Unlike the SHeS’Cap-PrEP study [21] that focused on AGYW and ABYM who tested HIV negative at the selected pre-exposure Prophylaxis (PrEP) SDPs (health clinics, school-based and community-based centers), this study will focus on AGYW and ABYM with a positive HIV test outcome. These will include quantitative analysis of routine program monitoring data; monitoring of linkage to and retention in HIV care among AGYW and ABYM who test HIV-positive in selected SDPs, and in-depth interviews (IDIs) with AGYW and ABYM to describe the barriers to, and enablers of linkage to, and retention in HIV care. We will also conduct key informant interviews (KIIs) with healthcare providers involved in the implementation of the UTT program in the district.

The primary outcomes for this study are linkage to care within 14 days and retention in care at six months after HIV diagnosis. Linkage to care is defined as “the proportion of AGYW (15–24 years) and ABYM (15–35 years) per SDP per month who have been initiated onto ART as evidence by a record in their TIER.Net or for whom baseline CD4 results have been captured into their TIER.Net record within 0–14 days (within 2 weeks) of their HIV-positive test at enrolment.” Retention in care is defined as “the proportion of AGYW (15–24 years) and ABYM (15–35 years) per SDP per month for whom an entry has been captured into the National Health Laboratory Service (NHLS) for confirmed linkage at 6 months after their positive HIV test at enrolment.”

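### The objectives and the outcome clock presuppose a new diagnosis, but Table 1 asks only for a positive rapid test that day, so previously diagnosed people can enter the primary outcomes

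*Protocol article*

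**What the plan says.** All references are to the protocol article.

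- **Objectives.** Objective 1 concerns people "newly diagnosed with HIV who access HIV testing services in the uMgungundlovu district of KwaZulu-Natal", and objective 2 also names the newly diagnosed. Objective 3, which carries linkage and retention, is worded more widely: "Among HIV-positive AGYW and ABYM, to quantify linkage to and retention in HIV care across different service delivery models".
- **Study design.** "The primary outcomes for this study are linkage to care within 14 days and retention in care at six months after HIV diagnosis". Linkage credits people "who have been initiated onto ART as evidence by a record in their TIER.Net" or with a captured baseline CD4 result, and the sentence closes with a window of 0 to 14 days from the positive test at enrolment.
- **Table 4.** The 14 days are attached directly to the ART record, and the CD4 route is given one month. The table also places the HIV diagnosis at enrolment.
- **Study population and recruitment, Table 1.** The serostatus inclusion is "Be seropositive based on HIV rapid test results on the day of recruitment", and the only serostatus exclusion is "Test HIV-negative on the day of recruitment". The cohort is described as "Newly enrolled AGYW and ABYM who test HIV-positive in a participating SDP on the day of enrolment during the 12 months data collection period".
- **Recruitment point.** "Participants will be enrolled in the study as they await HIV testing".
- **Data analysis.** The Cox model runs from the date of the positive test to ART initiation.

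**The concern.** A positive rapid test today does not establish that the person was undiagnosed yesterday. The outcomes make sense only if it does. Linkage within 14 days, retention at six months and time to ART initiation all count from the enrolment test as if HIV care could not have begun before it.

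The article prints its eligibility table in full, and that table does not define the population named in objectives 1 and 2. This is therefore a mismatch between stated parts of the plan rather than a detail left to another document. At stake are the linkage and retention proportions by service model, which are the study's main product, and the comparison between models if previously diagnosed people are spread unevenly across them.

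**Working it through.** **1. What each outcome does with someone already on ART**

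- *Linkage.* ART initiation precedes the window. Study design ends its definition with 0 to 14 days, and Table 4 ties the ART record to 14 days, so the natural result is not linked. The result is linked only if an old TIER.Net record is credited regardless of date, or if a newly captured CD4 result is accepted as a baseline one.
- *Retention.* A laboratory or TIER.Net entry at six months would reflect care that began before enrolment.
- *Time to ART.* Initiation date minus test date is negative. The article states no rule for this.

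For someone diagnosed earlier but never linked, the values can be computed, but they are counted from a repeat test and not from diagnosis.

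**2. The plan's own figure**

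Table 2 gives 11 clusters of 50 per model, ICC 0.01, 0.62 versus 0.72, alpha 0.05 and power 0.89.

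- Design effect = 1 + 49 × 0.01 = 1.49; effective n per model = 550 / 1.49 = 369.1.
- Normal-approximation power is 0.895 one-sided, which agrees with 0.89, and 0.825 two-sided.

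The article does not state sidedness. That is a separate matter; the two-sided 0.825 serves here only as a base.

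**3. Illustration of size**

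Inputs:

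- p = 0.62, the provincial average in the Sampling section, assumed here to be the true rate among new diagnoses.
- r = share of enrolled people already on ART. The documents give no value, so r is an assumption.

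Observed linkage = p(1 − r) if they count as not linked, and p(1 − r) + r if they count as linked.

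| r (assumed) | Counted not linked | Counted linked |
|---|---|---|
| 10% | 0.62 × 0.90 = 55.8% | 0.558 + 0.10 = 65.8% |
| 20% | 0.62 × 0.80 = 49.6% | 0.496 + 0.20 = 69.6% |

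*Equal shares in both models.* A true 10-point difference becomes 10 × (1 − r), which is 9 points at r = 10% and 8 points at r = 20%. Two-sided power falls from 0.825 to 0.706 and 0.587 if they count as not linked, or to 0.764 and 0.694 if linked.

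*Unequal shares, true rate 62% in both models.* An excess share d in one model creates a false difference of −0.62d (not linked) or +0.38d (linked). For d = 10 percentage points this is −6.2 or +3.8 points. For an assumed 20% against 5%:

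- not linked: 0.496 − 0.589 = −9.3 points;
- linked: 0.696 − 0.639 = +5.7 points.

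The planned difference is 10 points.

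**The case against.** The case on the other side has substance.

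- **Objective 3 says HIV-positive, not newly diagnosed.** This stands: the direct contradiction is with objectives 1 and 2. For linkage and retention, the problem follows from timing both outcomes from diagnosis and taking the enrolment test as that diagnosis.
- **The definition is not freely ambiguous.** This largely stands. The 14-day window in Study design and Table 4 makes crediting an old ART record the weaker reading, so the not-linked figures deserve more weight.
- **No passage shows that such people come for testing.** This stands. A reader might infer that people already on ART do enter and are misclassified; the documents show only that they can. The introduction reports that 93% of women and 88% of men living with HIV knew their status in 2018. That shows a large pool of known positives, but not how often they re-test.
- **The shares are assumed.** This stands. A reader might also infer that the model comparison is biased by some definite amount, but neither r nor a difference in r between models has any source in the article.
- **Negative times are data handling.** This stands in part. ART initiation date is a listed variable, so such cases can be found. Whether they belong in the analysis at all is a question of population, and the article's eligibility table answers it by admitting them.
- **The study is non-randomised and exploratory.** True, but its stated purpose is to supply linkage rates for planning intervention studies, and those rates are what would be distorted.

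**Conclusion.** The point holds as a mismatch between the target population and the eligibility table, with consequences for both primary outcomes and the time-to-ART analysis. Followed as written, the plan can place previously diagnosed people in a linkage denominator, a retention outcome and a Cox model that have no valid value for those already on ART.

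Its size is unknown. If true linkage is 62% and 10% to 20% of those enrolled are already on ART, observed linkage would be 55.8% to 49.6% on the likelier reading, or 65.8% to 69.6% on the other. Both inputs are assumptions, and a share near zero would make the effect negligible. Bias between service models arises only if the shares differ, which is possible but not shown.

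A blanket exclusion at recruitment does not follow from the documents. People are enrolled while waiting for the test, when a records check may not be workable. Such an exclusion would also remove people diagnosed earlier but never linked, whom objective 3 may include.

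**What to change.** Align Table 1 and the objectives through the analysis set, before the primary analysis:

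1. Define the set for primary linkage, retention and the Cox model as people with no self-reported or documented positive HIV test, ART start or HIV-care record (TIER.Net or NHLS) dated before the enrolment test.
2. Report the number of previously diagnosed people by service model.
3. Analyse them separately, split into those already on ART and those diagnosed but never linked.
4. Give a sensitivity analysis in all who tested positive at enrolment.

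The cost is a somewhat smaller primary denominator and a look-back in routine sources that the study already uses. The restriction also relies on those records being complete. If completeness differs between service models, the restriction could select unevenly, and the all-positives analysis and the counts by model help to show this.

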### Sampling

#### Service delivery points (SDPs) and sample size for individuals to be enrolled

The criteria for selecting the 22 SDPs included in this study have been reported elsewhere [21], and the HIV testing number in these SDPs are >4000 clients per month. Published studies and previous surveillance data from KwaZulu-Natal province in South Africa demonstrate an average linkage to care rate of 62% post HIV testing. However, recent findings from a district neighboring uMgungundlovu, reported a linkage to care rate of 83% [23]. We assume the linkage to care rates in uMgungundlovu district municipality to be 10% higher than 62% reported from the province based on the possible impact of UTT on HIV uptake. Also, we intend to compare the three service delivery models (facility-based, school-based, and community-based) across the seven sub-districts in uMgungundlovu. Since the study is non-randomised (unmatched study) with purposive sampling, it will be exploratory in nature and will inform the rates of linkage to care based on the different SDPs to facilitate better planning for intervention studies.

Sample size calculations (Table 2) are illustrative of the power of the study design to detect difference in coverage by service delivery models and are based on the comparison of proportions between clusters of fixed sizes in each service delivery group at a specific time point (i.e., 6 months follow-up). The sample size was done for the comparison of mainly community versus facility service delivery models for all the participants with the assumption that the participants attending schools i.e., TVET colleges and High schools will be included in the facility and community-based arms. The number of clusters (SDPs) needed to detect a coverage difference between the community- and facility-based service delivery models with >80% power is 22 in total, translating to 11 in each model with 50 participants per cluster assuming an intraclass correlation coefficient (ICC) of 0.01 and significance level of 0.05 [24]. The sample and power calculation were done using Stata v14.2 [25]. The study will retain at least 80% power for a 20% dropout at 6 months of follow-up (m = 40 per cluster) and the design effect of 1.5 were deemed realistic for the study populations.

**Table 2 pone.0271942.t002:** Power and sample size for the comparison of service delivery model for the SHeS’Cap-Linkage study in uMgungundlovu district, KwaZulu-Natal, South Africa, 2021–2023.

### Data collection

Baseline quantitative data collection will commence simultaneously in all 22 participating SDPs using self-administered electronic questionnaires built into REDCap [26]. The enrolment and data collection processes are summarized in Fig 1.

**Fig 1 pone.0271942.g001:**
[figure not shown]
An illustration of the study activities for the SHeS’Cap-Linkage study in uMgungundlovu district, KwaZulu-Natal, 2022.

Secondary data sources, including routine data from facility-based health information systems, routine data from district-level TIER.Net, data from the National Health Laboratory Service (NHLS) and data from the South African Medical Research Council (SAMRC)’s Rapid Mortality Surveillance (RMS) containing monthly information about deaths registered by the South African Department of Home Affairs will be used to obtain information on linkage to and retention in care in the SDPs where this project will be implemented. The RMS, therefore, will be used to confirm that the individual considered as not linked to care or not retained in care was not deceased. Table 4 gives an overview of the outcome variables, and data sources and tools.

**Table 4 pone.0271942.t004:** Roles of outcome variables in the SHeS’Cap-Linkage study in uMgungundlovu district, KwaZulu-Natal, 2021–2023.

Outcome variables	Examples of variables	Data sources and tools
• Proportion of AGYW and ABYM who have initiated ART as evidenced by a record in their TIER.Net within 14 days or for whom baseline CD4 results have been entered into their TIER.Net record within 1 month of their HIV-positive test result at enrollment. (Primary outcome)	• Patient receipt of HIV test result.	• Routine data (Clinical charts, clinic HIV testing and tracking registers, patient folders and TIER.Net*) and questionnaire data as necessary.
	• Patient attendance at first clinic appointment after receipt of HIV result.	
	• Enrolled patients taking up same-day initiation onto ART at diagnosis	
	• Proportion for whom ART initiation is within 2 weeks of a CD4 test	
	• ART initiation date recorded in clinical stationery and/or TIER.Net	
• Proportion of AGYW and ABYM for whom an entry has been captured into their TIER.Net record at 6 months after their positive HIV test at enrollment. (Primary outcome)	• Patient attendance at clinic as per contemporary NDoH guidelines at 6 months after HIV diagnosis	• Routine data (Clinical charts, clinic HIV testing and tracking registers, patient folders and TIER.Net*)
	• NHLS records of samples received at NHLS laboratory, as per contemporary NDoH guidelines (e.g., repeat CD4 or Viral Load results every 6 months)	• NHLS records
		• RMS
		• Baseline and follow-up questionnaires
	• TIER.Net records at facility of NHLS results recorded within 1 month of the date each sample was sent	
	• Viral load suppression at 6 months	
• Proportion of enrolled participants testing HIV-positive and not yet initiating ART who are not retained in HIV care at 6 months after HIV diagnosis at initiation		• Routine data (Clinical charts, clinic HIV testing and tracking registers, patient folders and TIER.Net*)
• Further description of participants’ health seeking behaviour	• Participant experiences of seeking HIV testing and care prior to date of HIV diagnosis at enrolment in this cohort.	• In-depth interviews (IDIs)
	• Proportion of patients who are not retained in care after initiating ART	
• Clinic processes and data quality to support linkage to and retention in care.	• Completeness and location of post-test initiation (clinic/community/schools)	• Routine data (Clinical charts, clinic HIV testing and tracking registers, patient folders and TIER.Net*)
• Association between SDPs processes and linkage to and retention in care and psychosocial factors including social support and age-appropriate disclosure, health literacy and beliefs, HIV stigma and expectations of health services	• Proportion initiating ART immediately after a positive HIV test at SDPs	• Baseline and follow-up questionnaires

*TIER.Net is an electronic patient management system used to capture patient-level data on HIV management in South Africa. **NHLS:** National health laboratory system; **RMS:** Rapid Mortality Surveillance; **AGYW:** Adolescent girls and young women; **ABYM:** Adolescent boys and young men; **ART:** Antiretroviral therapy; **SDPs:** Service delivery points.

A health system/facility assessment survey tool [27, 28] will be used to collect both quantitative and qualitative data. The qualitative data will focus specifically on healthcare providers’ perceptions on the implementation of UTT. Healthcare providers at each SDP will be approached by interviewers and depending on availability, an appointment will be secured. This is necessary not to disrupt the daily functioning of the SDPs. In addition, HAST and HIV service managers in the district health team will also be invited to contribute to the semi-structured interviews. Given this study’s emphasis on strengthening the quality and use of routine data, we will use the Performance of Routine Information Management (PRISM) framework [29] to structure our health system assessments. An example of how the PRISM framework and tools [30] have been customised in a particular setting by the lead author is described elsewhere [31]. The health system assessment tool has been field tested, refined and used in another study [23].

Health system readiness data relevant to the following domains will be collected. Domains include readiness to implement new policies and systems, leadership and governance, clinical processes (e.g., package of care delivered, integration with TB and other services, monitoring and evaluation/ information management, clinical oversight), drug supply and support services management (e.g., laboratory services), human resource management, and financial management.

We will also collect qualitative data using IDIs and KIIs. IDIs will be undertaken with a subset of 90 enrolled male and female participants, to contribute to a nuanced understanding of the drivers and dynamics of linkage to and retention in HIV care, including the mechanisms (reasoning and decision-making) and context (individual, structural social and health systems factors) that influence AGYW’s and ABYM’s uptake of HIV treatment and care services to describe the relative success of different HIV treatment service delivery models. In order to obtain wide-ranging responses, a maximum variation purposive sampling technique will be applied to include a varied representation of participants in terms of age, gender, marital status, employment status, geographic area and location of SDPs utilized. These will include:

At least one enrolled participant from each participating SDPParticipants who tested HIV-positive at participating SDPs who did and did not link to care within 14 days, and who did and did not remain in care at 6 months after their diagnosis, if non-linked participants can be reachedParticipants who enrolled in the study and responded to the baseline interview but did not test for HIV.

Furthermore, KIIs will be conducted with 22 purposively selected stakeholders including reproductive and healthcare providers at different sites and primary health care centers. The KIIs will focus on the barriers to, and facilitators of linkage to care, and perspectives of ways to improve the uptake of HIV treatment and care services to describe the relative success of different HIV treatment service delivery models. During the KIIs, process mapping will also be conducted to understand the processes and steps involved in the delivery of the services in each of the models. In this case, emphasis will be placed on the inputs, outputs, and outcomes. The duration of the IDIs, and KIIs will range from 60–120 minutes depending on how the discursive and interactive process unfolds.

